### Trial Design

This study will be a multicenter, randomized, single blind clinical trial with three treatment groups (EA, counseling, and combination therapy). The flow chart in **Figure 1** shows more details regarding the clinical procedures. This study protocol has been approved by the Ethics Committee of the First Affiliated Hospital of Guangzhou University of Chinese Medicine, Affiliated Brain Hospital of Guangzhou Medical University, Guangdong Provincial Hospital of Chinese Medicine, and Guangdong Sanjiu Brain Hospital (NO. ZYYECK YJ [2019] 068).

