### Blinding

As a single-blinded trial, only outcome evaluators and statistical analysts will be blinded to treatment group. Evaluators and statistical analysts will not be allowed to participate in the treatment process of subjects and will be forbidden from knowing the grouping of subjects. Trial grouping information will be open to subjects, physicians, and data collectors. The analysts will generate a randomized sequence, only known by him or her, to allocate subjects accordingly to ensure the randomization of the grouping. The analyst will be responsible for the preservation and confidentiality of information and data and will prepare a backup of both electronic devices and paperwork. Special personnel will be in charge of those data and documentation. In addition, to ensure strict implementation of the blinded method in the test and reduce the bias of conclusions, physicians (psychologists and acupuncturists), outcome evaluators, data collectors, and statisticians will all be independent of each other and will have no communication during the test.

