###  Outcome Measures

The primary outcome measure is the HAMD-17 and BDI-II. Evaluation timelines are set as: before treatment, and the second, fourth, and sixth weeks of the treatment. HAMD-17 and BDI-II are widely used in the diagnosis and outcome evaluation of depression. The range of the HAMD-17 score is 0 to 52, with 25 scores or more indicating severe major depressive disorder, 18–24 scores indicating moderate, 7–17 scores indicating patients may have mild depression, and 0–6 scores indicating normal (36). The range of the BDI-II score is 0 to 63, with 29–63 scores indicating severe major depressive disorder, 20–28 scores indicating moderate, 14–19 scores indicating mild, and 0–13 scores indicating normal. The secondary outcome measures are SDS, SAS, and PSQI. The range of the SDS standard score is 0 to 100, with 72 scores or more indicating severe major depressive disorder, 63–72 scores indicating moderate, 53–62 scores indicating mild, and 0–53 scores indicating normal. The range of the SAS standard score is 0 to 100, with 70 scores or more indicating severe anxiety, 61–70 scores indicating moderate, 50–60 scores indicating mild, and 0–50 scores indicating normal. The range of the PSQI score is 0 to 15, where a lower score indicates better sleep quality. A score of 11–15 indicates poor quality of sleep, and a score of 0–5 indicates good quality of sleep (37). Evaluation time points are as follows: before treatment, and the second, fourth, and sixth weeks of the treatment, and a follow-up period. Participants will be followed up at 3, 6, and 12 months after treatment and will complete the SDS, SAS, and PSQI. In addition, functional MRI (fMRI) is an optional test under the attending physicians' supervision and instruction or depending on the patient's self-willingness. The fMRI, if included, will be performed in the resting state before the treatment and at the sixth week of treatment (38). The detailed procedures and parameters of fMRI are provided in **Supplementary File 1**. Also, the patient's blood samples and feces will be obtained twice before and after the treatment and will be used to build a biological sample bank, which could help with the research protocol moving forward.

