### Statistical Analysis

Statistical analysis will be performed by qualified statisticians in a blinded manner using Statistical Product and Service Solutions (SPSS) software (IBM Corporation, Version 21.0). An ITT analysis will be performed. The baseline comparability of the three groups will be assessed on demographic and clinical characteristics, as well as baseline data. Analysis of variance will be used to compare the mean changes between groups from baseline to each time point. The withdrawal of any subjects from clinical trials will be statistically described one by one. The missing data of a withdrawn patient will be randomly filled with the filling method based on the principle of multiple imputations (34). Continuous variables will be represented by mean ± standard deviation. The data before and after treatment in the group will be compared based on a paired *t*-test, and the comparison between groups will be performed using an independent sample *t*-test. When data are not normally distributed, a Wilcoxon rank sum test or Fisher's exact test will be performed. Multiple measurements of the same indicator at different times will use repeated measures data analysis of variance. Categorical variables will be expressed as frequency (%). Two-tailed *p* values < 0.05 will be considered as statistically significant. Safety will be assessed by adverse events and tabulations of adverse drug reactions and descriptive statistics will be performed. Age and intervention assessment are continuous variables, and their correlation will be analyzed using Pearson correlation coefficients. Treatment duration and gender are graded variables, and the spearman correlation coefficient will be used for the correlation analysis of the intervention assessment. To further evaluate the credibility of the blind method. We will evaluate the implementation of the blind method by trial participants' guesses about the allocation of treatment plans, that is, forcing evaluators and statistical analysts to guess the groups to which the subjects are assigned, and then calculate the Blinding Index Scale based on the guess results (39). In order to balance the heterogeneity of patients from different research centers, we will first analyze the differences between the clinical effects of different interventions in each subcenter. If the conclusions of the subcenters are consistent, there will be no central effect. If the conclusions of the sub-centers are inconsistent, a logistic regression analysis will be performed, and the center will be adjusted as a covariate to analyze the results of interventions and clinical assessment (40, 41).

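### Two primary scales, three visits and three unranked between-group methods, all judged at p < 0.05, leave the false-positive rate above 5% if any one significant result counts as success

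*Protocol article*

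**What the plan says.** **Arms.** Trial Design describes a trial "with three treatment groups (EA, counseling, and combination therapy"), so there are three pairwise contrasts.

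**Primary outcome.** Outcome Measures states: "The primary outcome measure is the HAMD-17 and BDI-II". For these scales, "Evaluation timelines are set as: before treatment, and the second, fourth, and sixth weeks of the treatment". No visit is singled out, and nothing says whether success on one scale is enough.

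**Tests.** Statistical Analysis names three between-group methods:
- "Analysis of variance will be used to compare the mean changes between groups from baseline to each time point";
- "the comparison between groups will be performed using an independent sample" t-test, with no visits named;
- repeated-measures ANOVA for serial measurements of the same indicator.

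It does not say which is the primary analysis, or whether the t-tests depend on the ANOVA result.

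**Significance.** One rule covers every test: two-tailed p "values < 0.05 will be considered as statistically significant".

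**Sizing.** Sample Size uses HAMD-17 alone, in one comparison of three means at α = 0.05 and power 0.90, to reach 46 per group.

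**The concern.** The trial was sized for one three-group test on one scale at 5%. The analysis text allows many tests of equal standing, each at 5%. A chance difference on either scale, at any visit, by any of the three methods, could be reported as the primary finding without departing from the text.

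Trial Objective rests its inference about EA on combination against counselling: if acupuncture has no effect, the two should do equally well. A false positive there would be read as evidence that EA is more than a placebo.

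**Working it through.** **1. Reproduce the stated sample size.** Inputs from Sample Size: means 5.7 (counselling), 5.26 (EA), 3.4 (combination); SDs 3.13, 3.11, 2.97; α = 0.05; power 0.90; dropout 10%.
- Pooled variance = (3.13² + 3.11² + 2.97²)/3 = 28.29/3 = 9.43, so SD = 3.07.
- Grand mean = 4.787. Sum of squared deviations = 0.834 + 0.224 + 1.923 = 2.981.
- Noncentrality λ = n × 2.981/9.43 = 0.316n. Power is 0.8997 at n = 41 and 0.907 at n = 42.
- For dropout, 42 × 1.1 = 46.2 and 41/0.9 = 45.6, so 46 per group is reproduced.

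The figure therefore matches a single three-group F test on HAMD-17 at 0.05.

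**2. Count the tests permitted.** 2 scales × 3 post-baseline visits × 3 pairs = 18. This is a maximum, because the t-test sentence names no visits. With ANOVA at each visit the count is 2 × 3 = 6. With one repeated-measures group test per scale it is 2.

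**3. Chance of at least one p < 0.05 when all arms are equal.** If the tests were independent, 1 − 0.95² = 9.75%, 1 − 0.95⁶ = 26% and 1 − 0.95¹⁸ = 60%. The last is too high, because the pairs share arms; with uncorrelated scales and visits, simulation gives 54%.

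The table is simulated at 46 per arm with normal data. The between-scale and between-visit correlations are set equal. They are assumptions, since the article gives none.

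| Assumed correlation | 18 t-tests, regardless of ANOVA | ANOVA at each visit, both scales (same if t-tests only follow a significant ANOVA) |
|---|---|---|
| 0.3 | 51% | 25% |
| 0.5 | 46% | 22% |
| 0.6 | 42% | 21% |
| 0.7 | 38% | 18% |
| 0.8 | 33% | 16% |

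- On change-from-baseline scores, the 18 t-tests give 49% at 0.3 and 42% at 0.8.
- One repeated-measures group test on each scale gives about 8–10% over the same range.
- Three pairs on one scale at week 6 give about 12%; on both scales at week 6, about 19–23%.

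**4. Check the remedy.** One scale, one visit, three-group F test at 0.05, then pairwise t-tests at 0.05 only if F is significant. Take 41 per arm (46 × 0.9 = 41.4).
- All arms equal: family-wise error about 4.9%.
- Two arms equal, third different: about 4.9% for the equal pair.
- Planned means and SDs: power 90% overall, 88% for combination v counselling, 76% for combination v EA.

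Without the F-test condition, the two pairwise powers at 41 per arm are 92% and 78%. By contrast, Bonferroni over 18 tests (α = 0.00278) would leave 73% and 47% even at 46 per arm.

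**The case against.** **The worst count is not the stated plan.** Statistical Analysis gives the per-visit comparison to ANOVA and serial measurements to repeated-measures ANOVA. It never schedules pairwise t-tests at each visit. This stands. A reader might infer a false-positive rate of roughly 40% outright, but that needs t-tests at every visit regardless of the ANOVA, an any-success rule, and correlations the article does not state. The kinder readings still give 8–10% and 16–25%.

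**A both-scales rule may be intended.** The wording, singular and joined by *and*, does not exclude it. Requiring both scales to be significant on the same pair and visit gives about 4–15% under the assumed correlations. That could bring the error near 5%, but the article does not state the rule.

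**An article leaves detail to the full protocol or SAP.** This is fair for a bare omission. Here, however, the article itself sets a dual primary outcome, unranked methods and a flat 0.05. Those choices are made, and they conflict with the single test used for sizing.

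**BDI-II as an unblinded self-report.** A reader might add this because Blinding says "Trial grouping information will be open to subjects, physicians, and data collectors". The article does not support it. It calls SDS a self-assessment scale and PSQI self-reported, but never says that patients complete BDI-II themselves. The point does not need it.

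**Conclusion.** The concern holds in this form: the primary analysis is not tied to one outcome, visit and test, and under any-success reporting the stated rule does not hold a 5% error rate. The size depends on the reading: about 8–10%, 16–25% or 33–51% for the three readings above, at 46 per arm with assumed correlations of 0.3–0.8. No single one of these figures is the trial's error rate, because the article fixes neither the reading nor the correlations. What is firm is that every any-success reading exceeds 5%.

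**What to change.** Before unblinded data are seen, amend Outcome Measures and Statistical Analysis as follows:
1. Name HAMD-17 as the single primary outcome at one time point. Week 6, the end of treatment, is one natural choice; Sample Size does not say which visit its means refer to.
2. Make BDI-II and the remaining visits secondary.
3. Make the three-group test the primary analysis, and test the three pairs at 0.05 only if it is significant at 0.05. With exactly three arms this is a closed procedure: if any two pairwise equalities are true then all three are, so α need not be split.
4. State the role of the repeated-measures ANOVA (for example, supportive).

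The cost is wording, plus the loss of primary status for BDI-II and the earlier visits. The sample size does not change, since it was already derived for this three-group test. Making the pairs conditional on it lowers power at 41 per arm from 92% to 88% for combination v counselling and from 78% to 76% for combination v EA.

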### Observation Criteria That Would Stop the Trial

Fail to adhere to the treatment requirement;Cases with serious adverse events that are not suitable for continued treatment;Serious clinical complications that occur in other clinical trials;The progression of disease during treatment.

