### Counseling Group

Sub-threshold depressed participants will receive individual counseling (once a week for 6 weeks; 50–60 min a session). Counseling will be performed by licensed psychologists with more than 3 years' experience and will be conducted in the psychiatric department of the hospital. Before the trial, the psychologists will receive brief training in counseling and conduct counseling activities based on a treatment manual designed by *Mental Disorders* (35). It mainly includes two aspects: First, help participants analyze their own problems, inform them about the physical harm of psychological defects, and encourage them to overcome these factors. Second, encourage participants to do things of interest to increase excitement and improve emotional state.

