### Combination Therapy Group

Participants will receive 24 sessions of EA treatment (three times a week for 6 weeks; 30 min a session) combined with individual counseling (once a week for 6 weeks; 50–60 min a session). Treatment details are the same as the EA and the counseling mentioned above.

Patients will be discouraged from any extra treatment beyond this trial requirement. If this trial does not show an obvious effect after 2 weeks of treatment (HAMD 17 scale score maintained at 7–17 points), or a patient's symptoms have worsened (HAMD 17 scale score > 17 points), we will then consider drug intervention to ensure the safety of the patients. At this point, participants will be forced to stop the trial, and relevant data will be analyzed for intention-to-treat (ITT). Prescription drugs will be assessed under the guidance of a psychiatrist. Such assessment will need to fully consider the physiological characteristics of patients, including age, physical condition, drug tolerance, presence or absence of comorbidities, and prescribing based on guidelines for depression or relevant clinical consensus.

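### The planned correlation of treatment duration with outcome is confounded by outcome-related early stopping and cannot be read as a duration or dose effect

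*Protocol article*

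**What the plan says.** The Statistical Analysis section of the protocol article plans two sets of correlations with what it calls the intervention assessment. For age: "Age and intervention assessment are continuous variables, and their correlation will be analyzed using Pearson correlation coefficients". For duration and gender: "Treatment duration and gender are graded variables, and the spearman correlation coefficient will be used for the correlation analysis of the intervention assessment". It does not define treatment duration or the intervention assessment, and it gives no purpose for the correlations.

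The length of treatment is the same in all arms. EA, alone or in the combination arm, is given "three times a week for 6 weeks; 30 min a session". For the counseling arm: "Sub-threshold depressed participants will receive individual counseling (once a week for 6 weeks; 50–60 min a session".

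The last paragraph under Combination Therapy Group says when treatment ends sooner. The first trigger is: "If this trial does not show an obvious effect after 2 weeks of treatment (HAMD 17 scale score maintained at 7–17 points". The second is: "a patient's symptoms have worsened (HAMD 17 scale score > 17 points), we will then consider drug intervention to ensure the safety of the patients". The consequence follows: "At this point, participants will be forced to stop the trial, and relevant data will be analyzed for intention-to-treat (ITT". The section on criteria that would stop the trial adds "The progression of disease during treatment", along with non-adherence, serious adverse events and complications.

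**The concern.** If everyone is scheduled for six weeks, duration is not a design variable. It is something that happens to a patient after randomization, and here it happens largely because of the patient's score. A patient with little improvement by week 2 may be stopped, and so has both a short course and, probably, a poor final score. Correlating the two treats a consequence of poor response as if it were a cause.

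At stake is a secondary statement in the trial report. With a two-sided 0.05 threshold, the analysis could show that longer treatment goes with better outcome when duration has no effect at all. Readers might take that as support for longer courses of EA or counseling.

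**Working it through.** **Plan's own figure.** The article gives no figure for these correlations. The only plan number used is the total of 138 (46 per group), from Sample Size.

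**Structure, from the text alone.**
1. The planned course is six weeks in all three arms, so duration varies only through early stopping.
2. Entry requires HAMD-17 from 7 to below 17 (Table 1). Every participant therefore starts inside the 7–17 band of the first week-2 trigger and leaves it favorably only by falling below 7.
3. HAMD-17 is also a primary outcome (Outcome Measures), and stopped patients stay in the ITT analysis. The variable that shortens treatment is an early measurement of the outcome it would be correlated with.

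The week-2 paragraph stands under the combination arm but is worded for the trial's patients generally. It is read here as applying to all arms.

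**Size, with no duration effect.** Let a fraction p with the worst week-2 scores stop, let r be the correlation of week-2 with final score, and assume both scores are normal. The product-moment correlation of duration (2 or 6 weeks) with final score is then

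-r × φ(z) / √(p(1-p)), where z is the normal quantile at p.

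- p = 0.30, r = 0.4: φ = 0.348 and √0.21 = 0.458. The ratio is 0.759, giving -0.30.
- p = 0.50, r = 0.7: φ = 0.399 and √0.25 = 0.5. The ratio is 0.798, giving -0.56.

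Simulated Spearman values for p of 0.3 to 0.7 and r of 0.4 to 0.7 agree: -0.30 to -0.57.

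**Significance threshold.** |r| = t / √(t² + n - 2). For n = 138, t = 1.978, giving 1.978 / √(3.91 + 136) = 0.167. For one arm of 46, t = 2.015, giving 2.015 / √(4.06 + 44) = 0.29.

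**Simulated results, n = 138, no duration effect.** A negative sign for the score and a positive sign for improvement mean the same thing: longer treatment appears better.

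| Setting (assumed) | rho | p < 0.05 |
|---|---|---|
| Final score; rule always applied | -0.26 to -0.58 | 87–100% |
| Final score; 25–50% of those meeting the rule stop | -0.08 to -0.35 | 14–99% |
| Week-6 improvement; rule always applied; r = 0.5–0.7 | 0.17 to 0.34 | 51–99% |
| Week-6 improvement; 25–50% stop; r = 0.5–0.7 | 0.04 to 0.21 | 8–70% |
| Week-2 and week-6 scores uncorrelated | about 0 | 4–6% |

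The improvement rows assume a baseline correlation of 0.3 and a flat post-baseline mean of 5 to 9. A further set of runs on week-6 improvement used week-2 means of 7, 9 or 11 and r of 0.3 to 0.7, with half or all of those meeting the rule stopping. It gave only 0.01 to 0.11, with p < 0.05 in 2–25% of trials. If each stopped patient's last observed score were used, the flat-mean settings gave 0.11 to 0.48, even with uncorrelated scores. The plan names multiple imputation, so that last result is a side case.

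**The case against.** The strongest reply is that the link between stopping and score is looser than the simulations assume.

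- The text says that drug intervention will be considered and then that participants will be forced to stop, so how often the rule bites is unsettled.
- Non-adherence, adverse events and complications also shorten treatment and need not follow HAMD-17.
- Stopped patients may receive drugs. The simulations leave out any drug effect on later scores, which could shrink or alter the correlation.
- Treatment duration is undefined. If it means the assessment week, the stopping argument applies only indirectly.
- If the correlation is computed within arms of 46, the threshold rises to about 0.29, and a true -0.30 would be significant only about half the time.

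All of this stands as a limit on size. A reader might infer that a false duration finding is close to certain, or that the week-2 rule alone produces the correlation. The documents support neither. What the reply does not remove is the direction of the problem: on the ordinary meaning of duration, its variation comes from early stopping, and the stated reasons for stopping are in large part the outcome itself.

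The treatment comparison is assigned to analysis of variance, t-tests and repeated-measures analysis. No primary inference rests on the correlations. That is right, and it keeps the point minor.

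**Conclusion.** The point holds for treatment duration and is minor. The planned correlation is confounded by reverse causation. With no duration effect, rho with final HAMD-17 lies anywhere from near 0 to about -0.58, and the false-positive rate is above 5% in most plausible settings. The size rests on assumed stopping fractions, week-2/final correlations and consistency in applying the rule. The direction rests on the text.

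A reader might also infer that the age and gender correlations are wrong because they cannot show whether treatment works differently by age or gender. The documents do not support that. They give these correlations no such role, the objective is to compare three treatments, and the article does not say that arms are pooled. A prognostic description is legitimate, and an exploratory label can be left to the analysis plan. Calling gender graded is a labelling slip: Spearman's coefficient can still be computed on a binary variable, and the label changes no result.

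The primary comparison and the sample size of 46 per group do not depend on any of this.

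**What to change.** Delete the correlation of treatment duration with the intervention assessment. If duration is kept, report it descriptively by arm with the reasons for stopping, and state that it cannot be read as an effect of duration or dose. Describe gender as a nominal (binary) variable. Treatment-by-age and treatment-by-gender terms may be added as exploratory analyses, but they are an option and not a correction.

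The cost is a change of wording in the analysis text. It needs no new data, visits or patients. It does not touch the stopping provisions, and no change to them is proposed here.

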### Setting

Investigators will conduct the trial in four hospitals in Guangzhou, China. These four hospitals are: The First Affiliated Hospital of Guangzhou University of Chinese Medicine; Affiliated Brain Hospital of Guangzhou Medical University; Guangdong Provincial Hospital of Chinese Medicine; and Guangdong Sanjiu Brain Hospital.

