### Randomization

Independent statisticians will use the block randomization method with SAS version 9.4 (SAS Institute. Inc., Cary, NC) to create a randomization table for each hospital. Randomization numbers will be sealed in opaque, sequentially numbered envelopes, and sent to each participating hospital (26). Random number envelopes will be kept in a double locker. If the participant meets the inclusion criteria and voluntarily signs the informed consent, the clinical research coordinator will send the sealed random number envelopes to the physician in order, who will open the envelope and allocate the qualified participants to the EA group, counseling group, and combined therapy group according to the random number.

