### Sample Size

Sample size estimation uses a completely random design to compare multiple sample means. Target sample size was estimated using the PASS11 version, 1-β = 0.9, α = 0.05. According to a previous study (27), the mean of HAMD-17 in the psychological counseling group was 5.7, and the standard deviation was 3.13; the mean of HAMD-17 in the EA group was 5.26, and the standard deviation was 3.11; the mean of HAMD-17 in the combined therapy group was 3.4. The standard deviation was 2.97. To reduce the error, the target sample size was slightly enlarged, and a 10% dropout rate was estimated. Therefore, a sample of 46 participants will be the goal for each group in the proposed trial. A total of 138 patients will be aimed for in total.

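### Centre is adjusted for only if four small per-centre analyses disagree, and then by logistic regression, although the primary scores are continuous and randomisation is done within hospital

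*Protocol article*

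**What the plan says.** All references are to the protocol article.

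- **Setting:** "Investigators will conduct the trial in four hospitals in Guangzhou, China".
- **Randomization:** independent statisticians use block randomisation "to create a randomization table for each hospital". Hospital is therefore a stratification factor by design.
- **Outcome Measures:** "The primary outcome measure is the HAMD-17 and BDI-II". Severity bands are listed for both scales, but no responder, remission or other categorical endpoint is named.
- **Sample Size:** based on HAMD-17 means and SDs in the three arms. "Target sample size was estimated using the PASS11 version, 1-β = 0.9, α = 0.05". "Therefore, a sample of 46 participants will be the goal for each group in the proposed trial".
- **Statistical Analysis:** mean changes are compared by analysis of variance, with t-tests and repeated-measures analysis of variance also listed. "Two-tailed *p* values < 0.05 will be considered as statistically significant". The centre rule comes at the end of the section. Treatments are first compared inside each hospital. Then: "If the conclusions of the subcenters are consistent, there will be no central effect". Failing that: "If the conclusions of the sub-centers are inconsistent, a logistic regression analysis will be performed, and the center will be adjusted as a covariate".

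The article does not define what makes conclusions consistent.

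**The concern.** The rule has four separate weaknesses.

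1. **The trigger is weak.** Each hospital contributes a small fraction of a sample sized for 90% power overall. Four such analyses can differ by chance when the true effect is the same everywhere, and they can all be non-significant when centres differ.
2. **The inference is wrong.** Hospitals can agree on the treatment comparison and still differ widely in mean score. Agreement therefore says nothing about a centre main effect.
3. **The remedy does not match the trigger.** Differing treatment conclusions are a matter of treatment-by-centre interaction. A centre covariate adjusts for a main effect only.
4. **The model does not match the outcome.** Logistic regression needs a categorical outcome. HAMD-17 and BDI-II are sized and analysed as means, so a cut-point would have to be chosen, possibly after the per-centre outcome results have been seen.

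At stake is whether the centre adjustment is fixed in advance or depends on chance, and whether a centre-adjusted result can be produced from the plan as written.

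**Working it through.** **Inputs.** From Sample Size: HAMD-17 mean (SD) of 5.7 (3.13) for counselling, 5.26 (3.11) for electroacupuncture (EA) and 3.4 (2.97) for combination; 46 per arm; 10% dropout; α = 0.05; power 0.90. From Setting: four hospitals. From Statistical Analysis: two-tailed tests. Assumed, because the article gives no centre sizes: equal recruitment.

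**Step 1. The plan's own figure.** The pooled variance is (3.13² + 3.11² + 2.97²)/3 = 9.430, so the SD is 3.071. The squared deviations of the three means from 4.787 sum to 2.981. One-way ANOVA power uses the noncentral F distribution with λ = n × 2.981/9.430.
- n = 41: power 0.8997, and 41/0.9 = 45.6, so 46.
- n = 42: power 0.907, and 42/0.9 = 46.7, so 47.

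The stated 46 per arm is reproduced to within one patient.

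**Step 2. Size per centre.** 46/4 = 11.5, so 11 to 12 per arm per hospital before dropout.

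**Step 3. Power within one centre.** The three-group ANOVA has power 0.34 (n = 11) to 0.37 (n = 12). For pairs, the two-sided t-test has noncentrality δ/(SD√(2/n)), with the SD pooled over the two arms:
- Combination v counselling: δ = 2.30, SD 3.051; power 0.391 (n = 11), 0.423 (n = 12).
- EA v combination: δ = 1.86, SD 3.041; power 0.277, 0.300.

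**Step 4. How often four centres with identical true effects disagree.** If p is the per-centre power, P(disagree on significance) = 1 − p⁴ − (1 − p)⁴. For combination v counselling at n = 11, this is 1 − 0.023 − 0.138 = 0.839. If only direction must agree, p is replaced by q = Φ(noncentrality). For the same pair at n = 11, q = Φ(1.768) = 0.9615 and P(disagree) = 0.146. The rows for all three pairs are simulated, because the pairs share arms.

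| Reading of *consistent* | Chance of the inconsistent branch, n = 11 to 12 |
|---|---|
| Combination v counselling, p<0.05 | 84–86% |
| EA v combination, p<0.05 | 72–75% |
| Three-group ANOVA, p<0.05 | 79–82% |
| All three pairs, p<0.05 | 94–95% |
| All three pairs, direction only | 88–89% |
| Combination v counselling, direction only | 12–15% |

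The direction-only figure for all three pairs is high because EA and counselling differ by only 5.7 − 5.26 = 0.44 points. If no treatment differs at all, a single significance test still disagrees across centres with probability 1 − 0.95⁴ − 0.05⁴ = 0.19.

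**Step 5. Cost of leaving centre out.** This was simulated with 4,000 trials per setting, about 41 completers per arm (10, 10, 10 and 11 across centres) and the same treatment effect in every centre. The article gives no between-centre SD, so a range of 0 to 3 points is assumed.

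| Between-centre SD | Power, no centre | Power, centre in model | Type I error, no centre | Type I error, centre in model |
|---|---|---|---|---|
| 0 | 0.90 | 0.90 | 0.05 | 0.05 |
| 1 | 0.88 | 0.90 | 0.04 | 0.05 |
| 2 | 0.82 | 0.90 | 0.02 | 0.05 |
| 3 | 0.69 | 0.91 | 0.01 | 0.05 |

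**The case against.** Four points can be made for the plan.

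- **The main analysis may not change.** A reader might infer that the logistic model takes over as the primary analysis. The text does not say so. The analysis of variance is stated without condition, and the logistic step may be a supplement. This stands: the article leaves open whether it replaces or supplements. On either reading, the step still needs an endpoint that the article does not name.
- **The fallback may be uncommon.** A reader might infer that the inconsistent branch is the usual outcome. That holds if conclusions are judged by significance, or by the direction of all three pairs. It does not hold if only the direction of combination v counselling counts (12–15%). So the frequency is not settled. What is settled is that the trigger is undefined and unreliable.
- **Omitting centre does not inflate false positives.** A reader might infer the opposite from unadjusted standard errors. Step 5 shows the error is conservative. Entry HAMD-17 scores are restricted and the analysis of variance is on change from baseline, both of which may limit centre differences. At a between-centre SD of 1 point or less, about 2 percentage points of power are lost.
- **Cut-points exist.** Outcome Measures prints bands, such as 0–6 for normal on HAMD-17 and 0–13 on BDI-II, so a cut would not have to be invented. They are described as severity categories and not made an endpoint. Any such cut discards information, though how much cannot be fixed while the cut is unspecified.

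That the article condenses a fuller document is no answer here. The rule, the inference drawn from agreement and the model are all stated in it.

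**Conclusion.** The point holds. The plan makes adjustment for a stratification factor depend on an undefined comparison of four underpowered analyses. It treats their agreement as evidence of no centre effect, which it is not. It then prescribes a model that does not fit the continuous primary scores and has no categorical endpoint named for it.

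With identical true effects, equal centres of 11 to 12 per arm and the plan's own means and SDs, chance alone triggers the fallback in about 12–15% to 94–95% of trials, depending on how *consistent* is read. On significance for the largest planned difference, the figure is 84–86%. Unequal recruitment would leave the smaller centres with less power still.

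The harm in the unadjusted branch is lost power only, from 0.90 to 0.88, 0.82 and 0.69 at assumed between-centre SDs of 1, 2 and 3 points. The documents do not support a claim of inflated type I error, nor a claim that the primary analysis necessarily becomes logistic.

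**What to change.** Replace the two-branch rule in Statistical Analysis as follows:

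1. Include centre as a fixed factor in the linear model for HAMD-17 and BDI-II in every between-group analysis, whatever the per-centre results show.
2. Report per-centre estimates and the treatment-by-centre term descriptively.
3. Delete the sentence that infers no centre effect from agreement, and delete the logistic regression for these outcomes.

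The cost is a change of wording and 3 degrees of freedom (four centres minus one). No extra patients are needed: with centre always in the model, simulated power stays at 0.90–0.91 and type I error at about 0.05 across the assumed range.
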